### Randomization

We define the herbal medicine as PBC or RBS under the criteria of Chinese Pharmacopoeia of 2010 version. The combined herbal drugs, such as relieving heat and calming liver Yang, decreasing wind and dispersing phlegm, loosing the bowels, are also under the criteria of Chinese Pharmacopoeia of 2010 version. Within 6 h from the onset, participants will be assigned at random to one of three treatment groups with a ratio of 1:1:1: (1) Group A: RBS, stasis-breaking herbal medicine (8 herbals); (2) Group B: PBC, herbal medicine without stasis-breaking herbal medicine (6 herbals) and (3) Group C: placebo comparator, only placebo. Randomization is generated and stratified in blocks of six by PROC PLAN process using the SAS software version 9.13. Stratified block randomization is concealed using a sequentially numbered and opaque envelope. The number of each group will be in balance within research centers and by the baseline NIHSS severity (≤17 vs. >17), age (>18 years) and hemorrhagic location (basal ganglia vs. all other), patients’ sex, baseline Glasgow Coma Scale, duration from onset to the first CT scan.

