### Follow-up and outcome evaluation

Clinical assessments are performed at enrollment; at 24 h after the onset of symptoms; on the 10th day after admission; and on the 90th day after the stroke. During the follow-up period, the following scales will used:the GCS assessing the level of consciousness according to the score ranging from 15 (normal) to 3 (deep coma);the NIHSS measuring neurologic deficit according to the score ranging from 0 (normal) to 42 (coma with quadriplegia), the mRS evaluating functional independence, the BI assessing the ability of daily life. More detailed information about the schedule of study visits is shown in Table 3.

**Table 3 Tab3:** Study visits

Assessment method	Screening	Onset (0 h)	24 h	10–14 days	90-day follow-up
Patient population	W	–	–	–	–
History	W	–	–	–	–
Physical examination	W	W	–	–	–
CT/CTA	W		W	W	–
Confirmation of entry criteria	W	–	–	–	–
Signing consent form	W	–	–	–	–
Serum and urine test	W	–	–	–	–
Concomitant medication or treatment	W	W	W	W	W
GCS	W	W	W	W	–
NIHSS	W	W	W	W	W
BI	W		–	W	W
mRS	–	–	–	W	W
Adverse events	w	w	w	w	W
Summary of patient	–	–	–	–	W

*CT* computed tomography, *CTA* computed tomography angiography, *NIHSS* National Institutes of Health Stroke Scale, *mRS* modified Rankin Scale, *BI* Barthel Index, *GCS* Glasgow Coma Scale

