### Secondary outcomes

Three secondary clinical efficacy outcomes are included as follows: (1) death owing to any cause on the 14th day; (2) disability as defined by mRS score ≤2 on the 90th day; and (3) change in NIHSS score at the 24th hour after the onset of symptoms.

In the study two technical efficacy outcomes are included as follows: (1) volume of hematoma growth as measured by a CT scan at 24 ± 3 h after onset of symptoms compared with the baseline CT scan; (2) recurrent bleeding measured by CT scan on 10 days after drug administration.

Two study safety outcomes are included as follows: (1) all serious adverse events; (2)hematoma growth at 24 ± 3 h.

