### Statistical analyses

All analysis are by intention to treat with a beta level of 0.10 and an alpha level of 0.025 (Type I and Type II error). The primary outcome is the percent change in the volume of the hematoma measured by a CT scan at 24 ± 3 h after the onset compared with the baseline CT scan. The volumes of the hematoma measured by a CT scan will be analyzed using generalized linear mixed models. The subjects and the readers (two neuroradiologists) will be defined as random effects, and the baseline volume of hematoma, the time from the onset to CT scanning, and the time from CT scanning to study intervention will be defined as fixed-effect covariates. The percentages of changes in the volume of hematoma are transformed to normality and eliminate negative values via logarithmic transformations. Comparisons will be made between the two treatment groups with placebo using Bonferroni’s method with a threshold of significance of 0.0167. The threshold of significance for all other comparisons was 0.05. Subjects died before finishing the follow up will be assigned the worst possible scores for measures of neurologic deficit and function prognosis. Regarding surviving subjects with missing outcome data, the last visit will be carried down. The scores on mRS will be analyzed in a cumulative logit model, with statistical adjustment for age, the baseline hematoma volume, the site of hemorrhage, and the baseline neurological status. The scores on the BI and NIHSS will be analyzed with Wilcoxon rank-sum tests. The difference of the frequency of SAE in the three groups at 3 months will be analyzed with Fisher’s exact test or the Chi square test. All dates will be analyzed via SPSS software, version 21.0.

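### The listed outcome is change in NIHSS at 24 h, but the plan tests NIHSS scores with an unadjusted rank-sum test: valid, but it may waste the baseline data already collected

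*Protocol article*

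**What the plan says.** - **Outcome.** Under Secondary outcomes, the third of three clinical efficacy outcomes is "change in NIHSS score at the 24th hour after the onset of symptoms". BI is not among the outcomes listed there.
- **Test.** Under Statistical analyses: "The scores on the BI and NIHSS will be analyzed with Wilcoxon rank-sum tests". No covariate, stratum or baseline value is attached, and the variable is called a score, not a change.
- **mRS, in the sentence before.** It goes into a cumulative logit model "with statistical adjustment for age, the baseline hematoma volume, the site of hemorrhage, and the baseline neurological status". The model for hematoma volume also carries its baseline value.
- **Baseline data.** Table 3 marks NIHSS at every visit from screening on, and BI at screening, 10–14 days and 90 days. It shows no screening mRS.
- **Deaths.** Subjects who die before the end of follow-up "will be assigned the worst possible scores for measures of neurologic deficit and function prognosis".
- **Randomization.** Baseline NIHSS, cut at 17, is one of the factors on which the groups are to be balanced.

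**The concern.** The outcome is defined as a change from baseline, while the test is described for scores without baseline. These are different analyses, and the article does not say which will be run.

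NIHSS and BI are the clinical scales for which a baseline value of the same scale exists, yet they are the ones left unadjusted, while the mRS, which has no baseline value, is adjusted. If entry NIHSS predicts NIHSS a day later, a test that ignores it leaves predictable variation in the error term. What is at stake is the precision of the 24-h neurological comparison. The type I error is not at stake.

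**Working it through.** The article states no power or sample size for NIHSS or BI, so there is no figure of the plan to reproduce. The check asks how much a baseline-adjusted analysis gains over each reading of the planned test.

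**Inputs from the article**
- 285 evaluable participants, allocated 1:1:1: 285 / 3 = 95 per arm. This is used only as the plan's own evaluable count.
- Two-sided 0.05, the threshold for comparisons other than the primary ones.

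**Assumptions (not in the article)**
- A true shift of 0.3 SD in the 24-h score.
- A baseline to 24-h correlation ρ of 0.5, 0.7 or 0.85, with equal SD at both times.

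**Step 1: variances, with the variance of the 24-h score set to 1**
- Raw score: 1
- Change: 2(1 − ρ) = 1.00 / 0.60 / 0.30
- Baseline-adjusted: 1 − ρ² = 0.75 / 0.51 / 0.28
- Adjusted relative to change: (1 + ρ)/2 = 0.75 / 0.85 / 0.925

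Adjustment is thus never worse than change in this approximation, and the two converge as ρ approaches 1.

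**Step 2: normal approximation to power**

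Power ≈ Φ(0.3 / √(2v/95) − 1.96), with v the variance from step 1. With v = 1 the first term is 0.3 / 0.1451 = 2.07.
- Raw score: Φ(0.11) = 54% at every ρ
- Change: 54 / 76 / 97%
- Adjusted: 67 / 82 / 98%

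**Step 3: simulation of the rank methods** (4,000 two-arm trials of 95 per arm, bivariate normal)

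| Assumed ρ | Rank-sum on 24-h score | Rank-sum on change | Rank ANCOVA |
|---|---|---|---|
| 0.5 | 52% | 51% | 63% |
| 0.7 | 50% | 73% | 78% |
| 0.85 | 52% | 96% | 96% |

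These sit slightly below step 2, as expected for rank methods. Against the raw score the gain is 63 − 52 = 11, 78 − 50 = 28 and 96 − 52 = 44 points. Against change it is 63 − 51 = 12, 78 − 73 = 5 and 96 − 96 = 0 points.

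**Step 4: a rougher, more NIHSS-like case** (1,500 runs; integer score from 0 to 42, deaths set to 42, a shift of 0.41 SD, 95 per arm)

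Power for score / change / rank ANCOVA:
- ρ 0.5: 64 / 64 / 76%
- ρ 0.7: 64 / 84 / 87%
- ρ 0.8: 67 / 96 / 95%
- ρ 0.9: 66 / 100 / 99%

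Type I error was about 4 to 6% for all three methods. The pattern is the same as in step 3.

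**Step 5: change scores and the rule for deaths**

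Suppose a death is scored 42 and change is then taken. A patient who enters at 30 and dies has 42 − 30 = +12. A survivor who goes from 5 to 20 has +15 and ranks worse than the death. Ranking the 24-h score itself, with baseline as a covariate, keeps deaths at the bottom.

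**The case against.** The best defence is that the analysis section of a condensed article names a test without restating the variable. Since the outcome is defined as change, the natural reading is that change is what is ranked. Baseline then enters the analysis, and most of the loss disappears at high correlation. That stands: the large gap applies only if raw scores are tested. What remains is that the wording says scores, that change still costs about 12 points at ρ = 0.5, and that change sits awkwardly with the worst-score rule.

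A rank test is also a sound choice for a bounded, skewed scale with deaths at the worst value, and it holds its type I error. A reader might infer that the comparison is biased; neither the text nor the simulations support that.

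A reader might also infer that chance imbalance in entry severity passes unchecked into the comparison. The Randomization section says groups will be balanced on NIHSS at a cut of 17 and on baseline GCS, among other factors. This is partial protection, since a two-level cut leaves variation within each level, but it rules out the stronger statement.

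Finally, a reader might call this a key outcome and extend the power figures to BI. The article ranks NIHSS change as one of three secondary clinical efficacy outcomes, does not list BI as an outcome, and gives nothing on how screening BI relates to BI at 10–14 or 90 days.

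**Conclusion.** The point holds as a mismatch between a listed secondary outcome and its test, with an avoidable loss of efficiency. It is not a validity problem.

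Its size depends on which variable is ranked and on a correlation that the article does not give. Over assumed correlations of 0.5 to 0.85, rank ANCOVA gains roughly 11 to 44 percentage points of power over a rank-sum test of the 24-h score, and roughly 12 down to 0 points over a rank-sum test of change. These figures rest on 95 per arm, a 0.3 SD shift and a bivariate normal model; the NIHSS-like simulation with deaths at 42 shows the same pattern. For BI the gain is unquantified.

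Because the method is stated and the covariate is already collected, this is an improvement to a fixed choice, not a request for detail that an article leaves out.

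**What to change.** In Statistical analyses, state that 24-h NIHSS is compared between each active arm and placebo, either by a cumulative logit model with arm and baseline NIHSS (the model type already planned for the mRS) or by rank ANCOVA on baseline NIHSS. Keep the worst-score rule for deaths, and keep the Wilcoxon test as a sensitivity analysis.

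Reword Secondary outcomes and Statistical analyses so that both name the same variable: the 24-h NIHSS adjusted for baseline. BI may be handled in the same way with screening BI as the covariate, as an option.

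This is close to a free improvement. It needs no new data and no extra visits. The costs are slightly more analysis work and a model assumption (proportional odds, or linearity in the ranks), which the retained Wilcoxon test helps to check. The article reports 280 of 360 patients recruited and analysts blinded until completion, so at that stage the change could be made before the code is broken.

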### Lost-to-follow-up and missing data

It is supposed that there is no missing safety data on SAE, because of the careful observation and detailed records while in hospital. For surviving patients with missing outcome data, the last observation was carried forward. Regarding other incomplete primary outcome data, we will use multiple imputation to fill in missing data with standard statistical procedure.

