### CT scanning

At screening, the baseline CT scans are obtained immediately after arriving at treating hospital to identify intracerebral hemorrhage; the first follow-up CT scans are done at 24 h after the onset of symptoms (range 21–27) to assess hematoma growth; and the second follow-up CT scans are performed on 10 days (range 8–14) after drug administration. The hematoma volume is measured by ABC/2 Coniglobus formula (Kothari et al. 1996). Hematoma growth is operationally defined as an increase in the hematoma volume of >33 % as measured by image analysis on the 24 h CT in comparison with the baseline CT scan (Kothari et al. 1996) (if the first follow-up CT scan cannot be done within 24 h from the onset, a 48-h CT scan will be analyzed). Blinding for the two neuroradiologists is maintained through analyzation of digital CT data. Computerized planimetric techniques are used to calculate the hematoma volume to valuated the primary end point. In a previous study, the interobserver agreement of this method has been proven perfect (Xu et al. 2015).

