### Adverse event validation

All adverse events will be recorded during the stay in hospital and all serious adverse events will be recorded 90 days after onset. Clinical events committee, which are composed of four expert physicians independent of the research centers, will validate all adverse events. Relatedness categories are as follows: (1) primary disease-related: events obviously due to primary disease with no time relationship to the therapy, or medication. (2) concomitant disease-related: events due to diseases instead of the primary disease with no time relationship to therapy or medication; (3) TCM medicine-related: events obviously due to TCM medicine with no time relationship to other therapy;(4) medicine unknown: medicine related but unable to attribute a specific medicine; (5) individual difference-related: events have strong time relationship to individual constitution, whose allergic constitution are intolerant to traditional Chinese medicine (TCM); (6) other; and (7) unknown.

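### Read literally, the missing-data rule gives a survivor with no follow-up CT the baseline haematoma volume, that is 0% change and no growth

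*Protocol article*

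**What the plan says.** Two sections of the protocol article deal with missing outcomes.

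- *Lost-to-follow-up and missing data*: "For surviving patients with missing outcome data, the last observation was carried forward". The following sentence reads: "Regarding other incomplete primary outcome data, we will use multiple imputation to fill in missing data with standard statistical procedure".
- *Statistical analyses*: "Regarding surviving subjects with missing outcome data, the last visit will be carried down". This comes straight after the rule that gives patients who die the worst score on the neurological and functional measures.

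*Statistical analyses* defines the main endpoint as follows: "percent change in the volume of the hematoma measured by a CT scan at 24 ± 3 h after the onset compared with the baseline CT". On the earlier scan, *CT scanning* says: "At screening, the baseline CT scans are obtained immediately after arriving at treating hospital". The next scheduled scans are at 24 h (21–27 h) and about day 10. The same section lets a 48-h CT stand in when the 24-h CT cannot be done. Growth means an increase of more than 33%, and *Secondary outcomes* also lists it as a safety outcome.

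On serious adverse events (SAEs), the missing-data section states: "It is supposed that there is no missing safety data on SAE". The reason it gives is careful recording in hospital. *Adverse event validation* says "all serious adverse events will be recorded 90 days after onset", and *Statistical analyses* compares SAE frequency at 3 months.

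**The concern.** The word *other* in the multiple-imputation sentence implies that the LOCF sentence before it already covers some primary outcome data, namely that of survivors. The last haematoma volume before 24 h is the baseline volume. Carrying it forward makes the percent change exactly zero, which falls below the 33% threshold and counts as no growth.

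The stated aim is to find out whether the therapy can cause haematoma growth. Filling an unseen scan with the most reassuring plausible value shrinks any true difference. If patients in one arm miss the scan more often, it can also hide harm or create an apparent benefit.

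Two related points follow from the same section:

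- A survivor's missing day-90 mRS is replaced by the day 10–14 score, the only earlier mRS in Table 3. This ignores any change over the following months.
- The reason given for complete SAE data covers the hospital stay, while the comparison runs to 3 months.

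**Working it through.** **Inputs.** From *Sample size*: 285 completers, a 20% non-investigation rate, 360 randomised, and Table 4 values of 16% (RBS) and 38% (placebo). I treat the Table 4 values as proportions with growth, as the section's formula for proportions does. From *Randomization*: 1:1:1, so 120 per arm. From *Statistical analyses*: a pairwise threshold of 0.0167. The share of patients filled by LOCF is not in the article, so it is an assumption and is shown as a range.

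**The plan's own figure.** 285 / (1 − 0.20) = 356.25, that is 357, close to the stated 360. The 20% therefore means up to 0.20 × 360 = 72 patients without a primary outcome. Only survivors with neither a 24-h nor a 48-h CT would come under LOCF, so 20% is an upper case.

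**What LOCF returns.** Percent change = (baseline − baseline) / baseline = 0%. If a share m of an arm is filled this way, and those patients have the arm's true growth rate p, the recorded rate is p(1 − m).

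**Equal missingness.** Power uses the two-proportion normal approximation: Φ{[d − z·√(2p̄(1−p̄)/n)] / √([p₁(1−p₁)+p₂(1−p₂)]/n)}, where d is the difference, p̄ is the mean of the two rates and z is the two-sided 0.0167 quantile. LOCF keeps n = 120 with diluted rates. Observed cases keep the true rates with n = 120(1 − m).

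| m | Placebo | RBS | Gap (points) | Power, LOCF | Power, observed cases |
|---|---|---|---|---|---|
| 0 | 38.0% | 16.0% | 22.0 | 93.2% | 93.2% |
| 5% | 36.1% | 15.2% | 20.9 | 91.2% | 91.8% (n = 114) |
| 10% | 34.2% | 14.4% | 19.8 | 88.8% | 90.1% (n = 108) |
| 20% | 30.4% | 12.8% | 17.6 | 82.7% | 85.8% (n = 96) |

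Even with random and equal missingness, filling with baseline gives less power than leaving the patients out.

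**Unequal missingness** (the missing shares and the 50% rate are assumptions):

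| Missing, herbal / placebo | True harm, 50% vs 38% (12 points), recorded as | No true difference, 38% in both, recorded as |
|---|---|---|
| 6% / 2% | 47.0% − 37.24% = 9.8 points | 0.38 × 0.04 = 1.5-point benefit |
| 15% / 5% | 42.5% − 36.1% = 6.4 points | 0.38 × 0.10 = 3.8-point benefit |
| 30% / 10% | 35.0% − 34.2% = 0.8 points | 0.38 × 0.20 = 7.6-point benefit |

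**Scale.** All of this is on the binary growth rate. The primary analysis is a mixed model on log-transformed percent change. Its distortion cannot be sized because the article gives no variance for that outcome.

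**SAEs.** No arithmetic applies. The reason offered ends at discharge, recording and testing extend to 90 days, and the abstract describes the 3-month contact as a postal questionnaire.

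**The case against.** The strongest reply is that LOCF was never meant for CT volumes. In *Statistical analyses* the LOCF sentence stands between the worst-score rule for deaths and the tests for mRS, BI and NIHSS, so its setting is the repeated clinical scales. The only missing-data sentence that names the primary outcome assigns it multiple imputation. That reading is possible. It does not remove the problem, because the missing-data section puts no such limit on LOCF and its *other* points the opposite way. On either reading, the rule for a missing 24-h volume needs to be stated.

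The second reply is that the 48-h CT comes first, so few patients may be affected. This stands. It is why the 20% row is an upper case and the lower rows matter as much. The 20% is an overall non-investigation allowance, not a forecast of survivors without either scan.

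A reader might go further in three ways that the article does not support:

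- *A real harm would be erased.* Only the most extreme assumed scenario (30% / 10%) nearly does this. At 6% / 2%, 9.8 of the 12 points remain.
- *Patients lost after discharge are coded as free of SAEs.* The article assumes complete data and states no such coding rule. The gap is that its reason does not reach day 90, when an SAE never reported would go uncounted in a simple frequency comparison.
- *Multiple imputation is reserved for deaths.* That is an inference. The article says only *other* incomplete primary data and does not define the group.

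**Conclusion.** The concern holds in limited form. As worded, the missing-data section places a survivor with no 24-h or 48-h CT under LOCF and so records 0% change on the outcome used to detect harm.

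The cost depends on how many such patients there are. With equal missingness, the loss of power relative to observed cases is 0.6 points at 5% affected (91.8 − 91.2), 1.3 at 10% (90.1 − 88.8) and 3.1 at 20% (85.8 − 82.7). Unequal missingness is the greater danger, since it can bias the safety answer in either direction, by an amount the article gives no means to predict. These figures assume that missing patients share their arm's growth rate, and they describe the binary outcome only.

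The day-90 mRS and SAE points are secondary but arise from the same section. This should be fixed. It does not by itself undermine the trial, because the text allows a milder reading and the 48-h scan limits the number affected.

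**What to change.** In *Statistical analyses* and *Lost-to-follow-up and missing data*:

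1. State that LOCF does not apply to the 24-h haematoma volume. After the 48-h CT fallback already in the plan, fill missing volumes by multiple imputation using arm, baseline volume, onset-to-CT time, 24-h GCS and NIHSS, and the day-10 CT.
2. Add a sensitivity analysis that counts death before the follow-up CT as growth. The worst-score rule for deaths covers neurological and functional measures and supplies no volume.
3. For survivors with missing day-90 mRS, use multiple imputation instead of the day 10–14 score. That score can serve as a predictor.
4. Beside the 3-month SAE comparison, report the in-hospital SAE comparison and the number without day-90 contact, by arm.

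The cost is wording and a little more programming. The imputation predictors are scheduled measurements in *CT scanning* and Table 3. The article reports 280 of 360 patients recruited and analysts still blinded, so the change can be made before the code is broken.

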### Data and safety monitoring

The Data Safty Monitoring Committee deliberates the data from intermediate safety analysis report and contacts the Trial Steering Committee. Interim results are extremely secret and once one of the three groups shows a distinct advantage over others, the committee will counsel to end the study ahead of schedule.

